#### Suggested indications for iFOBT use

Important symptoms and signs of CRC constitute a continuum in general practice [39]. Therefore, iFOBT may be relevant in patients presenting anaemia, change in bowel habits or abdominal pain when these are not eligible for urgent referral. Irritable bowel syndrome (IBS) is generally recommended to be diagnosed using Rome III Criteria with a minimum of diagnostic testing [43, 44]. However, as a positive iFOBT is considered equivalent to rectal bleeding, we found it relevant to recommend performing an iFOBT on patients undergoing evaluation for IBS. Finally, non-specific symptoms such as weight loss, loss of appetite and fatigue are vague symptoms that can be presented in a vast amount of diseases, including different cancer types. Thus, using iFOBT as part of the diagnostic workup of patients presenting non-specific symptoms may aid the GP in the diagnostic process.

#### Recommended actions on positive and negative test results

In this study, the iFOBT is used as a ‘rule in test’. An iFOBT value ≥ 50 μg/L is considered as positive and should be followed by urgent referral to colonoscopy. An iFOBT value ≤ 49 μg/L is considered as negative. As CRC has a low prevalence in general practice, a negative test result should not exclude CRC; a negative result should rather serve to guide the GP in the direction of the most appropriate diagnostic strategy. The iFOBT can also be repeated.

### Analysis of the iFOBT and determination of clinical cut-off

In the Danish screening programme, the iFOBT is analysed on OC-Sensor DIANA (Eiken Chemical Company, Ltd, Japan). In the CDR, the analysis is performed at the Department of Clinical Biochemistry at the Regional Hospital of Randers. All iFOBTs requested from general practice during the study period will be analysed using this existing infrastructure in parallel with the screening samples. iFOBTs are analysed continuously and done by staff blinded to colonoscopic findings.

Studies of iFOBT cut-off values have primarily been conducted in a screening setting [45–49]. The cut-off value in the Danish screening programme is set to 100 μg/L. To our knowledge, no studies have investigated an optimal cut-off value for patients presenting non-alarm symptoms of CRC. Small amounts of blood loss in faeces are normal, but no exact reference level exists [50]. On the other hand, small amounts of blood in faeces may also be indicative of CRC. A low cut-off value for blood in stools increases the number of false positive test results and consequently the number of performed colonoscopies and required resources, whereas a high cut-off increases false negative test results and thereby introduces a risk of delay in the diagnosis [31, 51]. In this study, we set the cut-off value to 50 μg/L. Thus, a value of <50 μg/L will be considered as negative and ≥50 μg/L as positive.

### Logistics

The iFOBTs will be packed in kits together with a patient instruction on how to correctly perform an iFOBT, a paper to facilitate collection of the stool test and a postage-paid envelope addressed to the Regional Hospital of Randers. The packing of iFOBT will be provided by a company with expertise from the screening programme. The iFOBT kits will be delivered to a regional distributor. From here, all GPs will get a box with 10 kits at the date of inclusion. Furthermore, GPs can order additional iFOBT deliveries during the study period. Thus, the access to iFOBT will be easy as the tests will be available in the GPs’ clinics.

Ordering of an iFOBT is done through WebReq, which is an online ordering system used by Danish GPs for requesting laboratory tests. The GP indicates why the iFOBT is required by ticking a simple box in the ordering system. It is possible to tick the indications from the clinical instruction and a space for other symptoms or signs which can be used if the test is requested on other indications. The patient’s iFOBT sample is sent to the Department of Clinical Biochemistry at Randers Regional Hospital for analysis. Test results are returned to the participating GPs electronically and automatically transmitted to the patient’s medical record.

### Outcomes

The uptake and clinical use of iFOBT in general practiceFrequency of each indication used for requesting iFOBT○ Indications are registered when the GP orders the test. It is possible to tick the indications from the clinical instruction, and a box for other symptoms.Rate and frequency of iFOBT use and characteristics of the patients included.The GPs’ action on a positive test result (≥50 μg/L)○ According to the clinical instruction, a positive iFOBT result should imply referral to colonoscopy.The GPs’ action on a negative test result (≤49 μg/L)○ This outcome will evaluate how patients with a negative test result are followed up.

The diagnostic value of using iFOBT in general practiceAge- and sex-standardised number and rates of positive tests (>50 μg/L)Overall positive predictive value (PPV) for having CRC when iFOBT is positivePPV of having CRC in relation to iFOBT cut-off

The clinical implications of using iFOBT in general practiceAge- and sex-standardised number and rates of urgent referral in the CPP for CRCAge- and sex-standardised number and rates of colonoscopiesAll findings of colonoscopy on patients with a positive iFOBT (all ICD-10 codes determined at colonoscopy)Age- and sex-standardised number of CRCs diagnosedStage distribution of all CRCs diagnosed (I–IV)

### Data collection

All citizens in Denmark are registered in the Danish Civil Registration System with a unique personal identification number (CPR number). This identification number is used in all national registers and enables accurate linkage between national registers [52]. Statistics Denmark will provide data on socioeconomic and demographic factors [53]. Data on iFOBT value and indications for use of iFOBT will be provided by the Department of Clinical Biochemistry at Randers Regional Hospital through the clinical laboratory information system research database [54]. Data on colonoscopy and comorbidity are extracted from the Danish National Patient Register [55]. Data on CRC diagnosis and disease stage are extracted from the Danish Colorectal Cancer Database.

### Sample size

Each included GP is estimated to request 1–2 iFOBTs per week. This estimate is based on a previous report investigating Danish citizens’ reasons for encounter with a GP [56]. When taking into account that the study is rolled out sequentially and the study period is 1 year, we expect that 33,600 iFOBTs will be performed during the study period. Unpublished data from the Danish screening programme reveal that 6–10 % of performed iFOBTs are positive (≥100 μg/L) depending on age and gender. As this study uses a lower cut-off value (50 μg/L) and the investigated population is symptomatic, we estimate that approx. 10 % of performed tests will be positive. Screening studies have shown that the PPV of having CRC when the iFOBT is positive is approx. 10 % [26, 28, 29]. Therefore, we estimate that 10 % of the patients with a positive test will be diagnosed with CRC. In total, we expect to find approx. 336 CRCs by the use of iFOBT during the study period. Approx. 800 CRCs are annually diagnosed in the CDR. Using an alfa of 0.05 and a power of 0.8, we will be able to show a significant reduction in stage IV cancers from 25 to 16 % of annual CRC. However, as a reduction of this scale is unlikely, the study may be underpowered for this secondary outcome.

### Statistical analysis

The study uses a cluster-randomised stepped-wedge design [40]. Therefore, analysis of data will follow the recommendations for this study design. Each general practice will serve as a control until crossing over to intervention. As iFOBT is not available to Danish GPs before they are included in the study, it will not be possible to compare the use before and after inclusion. However, we will be able to evaluate the dissemination of the test in general practice.

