### Setting and study population

The study will be performed in the Central Denmark Region (CDR), which is one of five regions in Denmark. The CDR covers approx. 1.2 million inhabitants, 381 general practices, 836 GPs and 19 municipalities. In each municipality, the GPs are organised in units (except for the GPs in the island municipality of Samsø that are included in the unit of Aarhus). Each unit is headed by a chairman who represents the GPs of the municipality. The GPs in Denmark own their own clinic, and approx. 1550 persons are listed per GP. Clinics operate as either solo practices or partnership practices. Remuneration is based on a mix of capitation (25 %) and fee-for-service (75 %) based on a centrally negotiated collective agreement. The GP acts as a gatekeeper to specialised care in the secondary sector, and the citizens must contact the GP for medical advice unless in case of emergency. Approx. 10–20 % of all consultations in general practice ends up with a referral [38]. Nearly all citizens (99 %) are listed with a specific general practice, and the GP is remunerated on the basis of a contract with Danish Regions and must fulfil certain requirements for waiting time and access. iFOBT is available to Danish GPs only to a limited extent as part of the urgent referral for non-specific serious symptoms that might be cancer [39]. However, no logistic setup is available in general practice regarding ordering and analysing the test.

The study population constitutes the 836 GPs in the 381 general practices in the CDR and the individuals aged 30 years or more who are listed with these practices.

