### Design

The study uses a cluster-randomised stepped-wedge design [40]. This design allows us to roll out the study in large scale and to include all general practices in the CDR.

During the first seven months of the study period, each municipality and their appertaining GPs will be randomly and stepwise included in the study to receive intervention (Fig. 1). The intervention (see details later) consists of sending iFOBT kits and a clinical guideline to the GPs and to offer an optional continuous medical education (CME) session about CRC diagnosis. The invitation to the CME is sent to the chairman of the GP unit who will arrange the date and time of the meeting. The month in which the CME is arranged determines the date of inclusion for each municipality. Thus, the date at which a municipality is included is defined as the first working day of the month in which the CME is planned to be conducted. As the CME component is optional, the GP units can choose not to participate in the CME. These municipalities are included on the first working day in the month after confirmation of non-participation (Fig. 2). The specific date of the CME is flexibly arranged as the CME can be scheduled to take place on any of the first 7 months, depending on the preferences of the GPs in the municipality (in consideration of other arrangements targeting GPs in the municipality, availability of venue, etc.).

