**Fig. 1 Fig1:**
[figure not shown]
Stepped-wedge design used for the study. Most municipalities start out as usual care (C). Within the first seven months, all will cross over to intervention (I). Seven possible dates of inclusion are available; the 19 municipalities are randomly distributed between these

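### No concurrent control remains from month 7, and CRC number and stage are compared only with the period before iFOBT; the other four regions could supply a supplementary comparator

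*Protocol article*

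**What the plan says.** Under Statistical analysis: "Each general practice will serve as a control until crossing over to intervention". The caption of Fig. 1 adds: "Seven possible dates of inclusion are available; the 19 municipalities are randomly distributed between these". The Design section ties crossover to the month of the CME session (sentence cut short here): "the date at which a municipality is included is defined as the first working day of the month in which the CME is planned to". The last wave therefore starts at the beginning of month 7 of a one-year study.

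The subsection on clinical implications plans to compare the number of CRCs in the study period with the number found before iFOBT was introduced, and to treat stage distribution the same way. Colonoscopy rates are estimated before and after intervention. No other region is named as a comparator.

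The setting is the "Central Denmark Region (CDR), which is one of five regions in Denmark". Colonoscopy data come from the Danish National Patient Register, and CRC and stage from the Danish Colorectal Cancer Database. On the personal identification number the Data collection section says: "This identification number is used in all national registers and enables accurate linkage between national registers". On access to the test, the Setting section says that Danish GPs have it only to a limited extent and without a logistic setup. The Statistical analysis section puts it more strongly: "As iFOBT is not available to Danish GPs before they are included in the study".

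The Sample size section states that a fall in stage IV share from 25% to 16% is detectable with 80% power, calls a fall of that size unlikely, and concedes that "the study may be underpowered for this secondary outcome".

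**The concern.** For half of the study year nobody in the region is unexposed, so those months carry no concurrent contrast. What the clinical-implications subsection offers instead is historical. The Background mentions several initiatives aimed at earlier stage, and the laboratory section says that study samples are analysed alongside those of the national screening programme. If stage or CRC numbers were moving nationally, a before/after difference would credit that movement to iFOBT or hide a real effect.

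The plan's own data sources offer a way to remove changes that all regions share. At stake is whether the statements about CRC number, stage and colonoscopy rate can be attributed to the intervention.

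**Working it through.** **Inputs from the article.** 19 municipalities, seven start dates, 12 months, about 800 CRCs a year in the region, stage IV share 25%, alpha 0.05 (taken as two-sided), power 80%.

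**Assumptions not in the article.** Municipalities of equal size; waves of 3, 3, 3, 3, 3, 2, 2; immediate effect; no intracluster correlation in the main calculation; 2,400 to 4,000 CRCs a year in the other four regions together; a cancer database that covers all regions.

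**1. The plan's own figure.** An even spread over seven dates gives 3 control months of 12 on average, so 200 control and 600 intervention CRCs. The pooled share is (50 + 96)/800 = 0.1825. The null SE is √(0.1825 × 0.8175 × (1/200 + 1/600)) = 3.15 points, and the alternative SE is √(0.1875/200 + 0.1344/600) = 3.41 points. Power for 9 points is Φ((9 − 1.96 × 3.15)/3.41) = 79.6%. The stated figure thus reproduces with a crude split that ignores calendar time and clustering. The article does not say which split was used. A continuity-corrected calculation giving 337 per group, close to the 336 test-detected CRCs expected, fits as well.

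**2. Concurrent control time.** Municipalities still under control in months 1 to 6 number 16, 13, 10, 7, 4 and 2, then none. That is 52 of 228 municipality-months (22.8%), or about 182 of 800 CRCs. The exposed share is 176/228 = 0.772.

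**3. Stepped wedge with month effects.** Linear model, variance 0.25 × 0.75 = 0.1875 per CRC, 800/228 CRCs per cell, multiplier 1.96 + 0.84 = 2.80.
- Month effects: SE 5.08 points, detectable 14.2 points; power for 9 points Φ(9/5.08 − 1.96) = 43%.
- Month and municipality effects: SE 5.98 points, detectable 16.8 points; power 32%.

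A variant with a mean share of 0.21, and either intracluster correlations of 0 to 0.05 or fixed municipality effects, gives 13.4 to 15.8 points.

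**4. Difference-in-differences.** This sets the Central Denmark Region against the other four regions, study year against k preceding years, with M CRCs a year elsewhere and region-by-year SD σ:

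variance = 0.1875 × (1/800 + 1/(800k) + 1/M + 1/(Mk)) + σ² × (1 + 1/k) × (1 + 1/4)

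The result is divided by 0.772, because 22.8% of the region's study year is unexposed and the stepped-wedge figures refer to full exposure.

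Example with k = 1, M = 2,400, σ = 0: variance 0.1875 × 0.003333 = 0.000625, SE 2.50 points, × 2.80 = 7.0, ÷ 0.772 = 9.1 points. With σ = 2 points, 0.0004 × 2 × 1.25 = 0.001 is added: SE 4.03, × 2.80 = 11.3, ÷ 0.772 = 14.6 points.

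| Region-by-year SD (assumed) | One preceding year | Three preceding years |
|---|---|---|
| 0 | 8.6–9.1 | 7.0–7.4 |
| 1 point | 10.3–10.7 | 8.4–8.8 |
| 2 points | 14.3–14.6 | 11.7–11.9 |

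Detectable difference in percentage points, M from 4,000 to 2,400.

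**5. What the gain depends on.** If the Central Denmark Region is given its own free month effects, the outside regions add nothing: the SE stays at 4.95 points (intracluster correlation 0.01, cluster autocorrelation 0.8). The whole gain comes from assuming a shared time course.

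**The case against.** The quoted sentence is an ordinary description of a stepped wedge and is not wrong. Stage is a secondary outcome whose low power the article admits. An extra observational comparison might sit in a full protocol or analysis plan that is not shown. Two of the three aims, uptake and diagnostic value, gain nothing. All of this stands and limits the weight of the point. The comparator for CRC number and stage, however, is a choice that the article states.

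A simple before/after comparison of 800 against 800 CRCs is also nominally precise: √(0.1875 × 2/800) = 2.17 points, × 2.80 = 6.1, or 7.9 on the full-exposure scale. Its weakness is bias, since any national trend passes straight into the estimate.

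Two stronger readings are tempting. A reader might infer that practices not yet crossed over are the only comparator. The clinical-implications subsection contradicts this, because it supplies a historical one. A reader might also infer that leaving out the other regions makes the randomised contrast less precise. It does not: those regions were not randomised and can only add a separate observational estimate.

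The last objection is that one treated region and four controls make a fragile comparison. That stands too. At an SD of 2 points the advantage over 14.2 points disappears with one preceding year and is small with three, and with so few regions the 2.80 multiplier is optimistic. The documents also do not show that screening had the same timing or uptake in every region.

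**Conclusion.** The point holds in a limited form. There is no concurrent control for six of the twelve months, and CRC number and stage are compared only with an earlier period, so the comparison cannot separate the intervention from national change. The other regions offer a concurrent comparator from registers the study already uses.

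The gain in precision is conditional. Against 14.2 to 16.8 points for the stepped wedge, the difference-in-differences detects 7.0 to 9.1 points if regions share a time course exactly, 8.4 to 10.7 at a region-by-year SD of 1 point, and 11.7 to 14.6 at 2 points. These figures rest on assumed CRC counts elsewhere, equal municipalities and an immediate effect. It would be wrong to conclude that the added analysis rescues the stage outcome: only with little regional variation does it detect less than the 9 points that the article itself calls unlikely. Its firmer merit is that it removes trends common to all regions. The change is worth making, but it is a supplementary analysis and does not correct a fault in the randomisation.

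**What to change.** Keep the stepped-wedge comparison, with calendar-month effects, as the randomised analysis. In the clinical-implications subsection, replace the uncontrolled before/after comparison of CRC number, stage and colonoscopy rate with a difference-in-differences labelled supplementary and non-randomised. It would compare the Central Denmark Region with the other four regions, and the study year with preferably three preceding years. Show the pre-period trends by region, include region-by-year variation in the standard error, and describe screening activity by region where it can be obtained. State the detectable difference on the full-exposure scale, beside the stepped-wedge figure.

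The cost is a wider register extract and some analysis time, with no recruitment and no change to the randomisation. The price in validity is reliance on parallel regional trends with a single treated region, which the preceding years can probe but not prove. Limited iFOBT use elsewhere would dilute the contrast somewhat. The comparison does not serve the uptake or PPV outcomes, because the iFOBT data come only from the laboratory that serves this region.

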#### Evaluating the uptake and clinical use of iFOBT in general practice

The frequency of each indication used to order the iFOBT will be assessed using descriptive statistics. The development in rate and frequency of iFOBT use are assessed descriptively by illustrating the dissemination with the relation between time and use of iFOBT. One-way ANOVA is used to test for differences in the development of iFOBT use among different municipalities and among different general practices within each municipality. To facilitate comparison of the general practices, they are divided into: clinics where all GPs attended the CME (all-CME-clinics), clinics where at least one, but not all GPs, attended the CME (colleague-CME-clinics) and clinics where no GPs attended the CME (no-CME-clinics). Actions taken on positive test results are assessed by investigating if patients with a positive iFOBT have been referred to colonoscopy. Actions taken on negative test result are assessed by estimating the rate of patients with a negative test result that are referred for colonoscopy and/or has iFOBT repeated.

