**Methods/Design:**

The study uses a cluster-randomised stepped-wedge design and is conducted in the Central Denmark Region among 836 GPs in 381 general practices. The municipalities of the Region and their appertaining general practitioners will be included sequentially in the study during the first 7 months of the 1-year study period. The following intervention has been developed for the study: a mandatory intervention providing all general practitioners with a starting package of 10 iFOBTs, a clinical instruction on iFOBT use in general practice and online information material from the date of inclusion, and an optional intervention consisting of a continuous medical education on colorectal cancer diagnostics and use of iFOBT.

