## Methods/Design

### Aim

The aims of the study are to:Evaluate the uptake and clinical use of iFOBT in general practice after targeted courses for GPs in correct use of the test.Estimate the diagnostic value of iFOBT when used on patients presenting with non-alarm symptoms of CRC.Investigate the clinical implications of using iFOBT for case finding in general practice.

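### One-way ANOVA of iFOBT uptake has no defined response and no allowance for exposure time, practice size or correlation; on unadjusted totals it would mostly detect start month and practice size

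*Protocol article*

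**What the plan says.** The analysis of the first aim is in the protocol article under Evaluating the uptake and clinical use of iFOBT in general practice. It first promises a description over time: "The development in rate and frequency of iFOBT use are assessed descriptively by illustrating the dissemination with the relation between time and use of iFOBT". It then names one test: "One-way ANOVA is used to test for differences in the development of iFOBT use among different municipalities", and applies the same test to the practices inside each municipality. Everything else under that heading is descriptive. The next sentence forms three attendance groups: "To facilitate comparison of the general practices, they are divided into: clinics where all GPs attended the CME", followed by clinics where only some GPs attended and clinics where none did. It does not say which test, if any, compares these groups.

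Three design facts bear on this:
- **Staggered starts.** The Abstract says that municipalities "will be included sequentially in the study during the first 7 months of the 1-year study period". The Fig. 1 legend adds: "Seven possible dates of inclusion are available; the 19 municipalities are randomly distributed between these".
- **Unequal practices.** Setting and study population gives 836 GPs in 381 practices, some solo and some partnerships.
- **Optional CME.** Under Design, a whole GP unit may decline the CME, and its inclusion month is then set by a different rule.

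The opening paragraph of Statistical analysis promises to follow stepped-wedge recommendations but gives no model. It also says that iFOBT use cannot be compared before and after inclusion.

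**The concern.** One-way ANOVA compares group means of independent observations with similar variance. Request counts here come from practices of different size, observed for different lengths of time and grouped in municipalities. The text does not say whether the response is a count or a rate, whether it is per practice, per GP or per listed person, or whether time runs from the calendar or from inclusion.

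This is the only inferential test named for the first aim, which is to evaluate uptake "after targeted courses for GPs in correct use of the test". A difference produced by start month, clinic size or unmodelled correlation could be reported as a real difference in uptake, or read as evidence about the courses.

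**Working it through.** **1. Exposure by design.** With seven monthly starts in a 12-month study, step s has 13 − s months of exposure: 12, 11, …, 6. The Sample size section expects 1–2 requests per GP per week. At 1 per week, a GP in the first step makes 12 × 52/12 = 52 requests and a GP in the last step 6 × 52/12 = 26. That is a 2:1 ratio with identical behaviour.

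**2. The plan's own figure.** Mean exposure is (12 + 11 + … + 6)/7 = 9 months, or 9 × 52/12 = 39 weeks. Then 836 × 39 × 1 = 32,604 requests, within 3% of the stated 33,600. At 1.5 and 2 per week the totals are 48,906 and 65,208, which do not match. So the plan's expected total fits unequal exposure at about 1 request per GP per week. The simulations use that rate.

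**3. Municipality test.** Simulation of one-way ANOVA at the 5% level, 600 runs per scenario, with equal true use per GP everywhere.
- From the article: 381 practices, 836 GPs (836/381 = 2.19 per practice), 19 municipalities, 7 steps.
- Assumed: practice sizes of 1 + Poisson, scaled to 836 GPs and unrelated to municipality; gamma variation between practices with coefficient of variation (CV) 0.5, 0.8 or 1.2.

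| Response | CV 0.5 | CV 0.8 | CV 1.2 |
|---|---|---|---|
| Study-year total per practice | 96% | 68% | 34% |
| Study-year total per GP | 100% | 93% | 46% |
| Rate per GP-month since inclusion | 4.2% | 5.0% | 4.5% |

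If use builds up or falls off after inclusion, the rate-based test rejects in 5.2 to 6.0% of runs (CV 0.8). Because practice size was unrelated to municipality here, the false rejections on totals come from start month. If the mix of solo and partnership clinics differs between municipalities, size would add to them.

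**4. Practices within a municipality.** There are 381/19 ≈ 20 practices per municipality. With one value each, the error degrees of freedom are 20 − 20 = 0, so there is no test. GPs could be replicates only in partnerships. Nine monthly values per practice give 20 × 9 − 20 = 160 error degrees of freedom, but these are valid only if the months are independent. Simulation of one such municipality (20 practices, 9 months, 1 request per GP per week, equal true use, 1,000 runs):
- monthly counts per practice: 100% rejection, from size alone;
- monthly rates per GP, no autocorrelation: about 5%;
- monthly rates per GP, assumed month-to-month autocorrelation 0.3–0.6 with log-SD 0.3–0.5: about 25 to 91%.

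**5. CME groups pooled across the Region.** Further assumptions: 40% of GPs attend, and 4 of 19 municipalities decline. A solo clinic has one GP, so it can only be an all-CME or a no-CME clinic. The colleague-CME group therefore consists of multi-GP clinics.
- Totals per practice: 99.8%, 98% and 85% false rejection at CV 0.5, 0.8 and 1.2.
- Totals per GP: 11%, 7% and 5.5%. Dividing by size removes most of the inflation, so size is its main cause.
- Rates per GP-month: 4.0 to 5.0% when municipalities do not differ. With a municipality log-SD of 0.2 and 0.4 (CV 0.8), 7.7% and 11.8%.
- Under other assumptions (18 units, practice log-SD 0.5, 4 units declining), the rate-based figures are 13%, 19% and 24% at unit log-SD 0.2, 0.3 and 0.4. Across the assumptions tried, the range is about 6 to 24%.

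**The case against.** A reader might infer that the ANOVA is bound to declare false differences, and that the roll-out creates them for municipalities and CME groups alike. The article does not support that, for these reasons:
- **A rate is possible.** The sentence before the ANOVA, and the Outcomes section, speak of rate as well as frequency. On a rate per GP-month the municipality test keeps about 5%, so count data and staggered starts then do little harm. Nesting does not invalidate that test when the practice is the unit. This stands.
- **Summary measures are legitimate.** One rate or slope per practice, compared across municipalities, is an ordinary analysis. This stands for municipalities. It does not help the comparison among practices within a municipality, where one summary per practice leaves no replicate.
- **ANOVA for CME groups is only implied.** If they were compared within municipality, the start date would be shared and municipality variation would drop out: rates rejected in 4 to 5% of runs. Totals still rejected in 14 to 33%, from practice size. The CME problem is therefore size and clustering, not the roll-out.
- **Limited stakes.** The uptake analysis is otherwise descriptive, and nothing presents the CME contrast as randomised. This stands, and it limits the seriousness.
- **Detail may sit in a fuller plan.** This is fair for the definition of the response. But the article commits to a named method, and the general stepped-wedge statement cannot supply a substitute, since the article itself says that use before inclusion is not available for comparison.

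**Conclusion.** The point holds conditionally, and the method should be changed before analysis. As written, the ANOVA has no defined response and no term for exposure, size or correlation.
- **Municipalities:** about 34 to 100% false rejection on study-year totals; about 5% on a rate per GP-month since inclusion.
- **Practices within a municipality:** no valid test without treating monthly values as independent, and inflated error if they are autocorrelated, even on rates.
- **CME groups, if pooled across the Region:** totals are confounded by practice size; rates are modestly anti-conservative, about 6 to 24%, when municipalities vary.

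The 6–12 months of exposure and the unequal practice sizes come from the article. Variation between practices and municipalities, the size distribution, attendance, the number of declining units and the autocorrelation are assumptions. The percentages move with them. The dependence on the choice of response, the missing replicate and the tie between CME group and clinic size do not. The point concerns the uptake comparison only, not the diagnostic-value or clinical-implication analyses.

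**What to change.** 1. Define uptake as requests per GP per month since inclusion, or per listed person aged 30 or more if list sizes can be obtained.
2. Replace the ANOVA by a Poisson or negative binomial mixed model of monthly requests per practice, with a log-exposure offset, time since inclusion and calendar month as fixed effects, and random effects for practice and municipality. Report differences among municipalities and among practices through the corresponding variance components.
3. Adjust CME-group comparisons for number of GPs, compare colleague-CME clinics only with other multi-GP practices, and report the results as non-randomised associations.

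The cost is revised wording and slightly more analysis work. Requests are recorded in the online ordering system, and CME attendance is registered. Data collection does not name the number of GPs or listed persons per practice. The number of GPs is needed anyway to classify clinics by whether all or only some of their GPs attended. List size would be an additional request.
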